#### ***10.26 Laboratory Testing Procedures***

Specimens for analysis will be collected as described in the Schedule of Events at the time points indicated. Venipuncture will be performed by trained certified nursing assistants, nurses, nurse practitioners, or physicians and collection and handling per the manufacturer's recommendations. A central venous catheter may be utilized for all blood sampling if the patient currently has one. Samples will be collected and stored at -80°C for evaluation of other biomarkers related to inflammation, disease severity, and response to therapy.

Sample collection at weeks +2, +4, +8, +12, +16, +20, +24 (if dose increased at week +16) and +44 may be collected at LabCorp or at the participants home by phlebotomists from Phlebotek. Phlebotomists from Phlebotek will process samples and ship safety labs to Quest and the remaining samples to LI. Samples collected by Lab Corp will be process at LabCorp laboratory.

## **Specimen Handling and Storage**

### Stored Plasma, Urine and Serum Sample Directions

**Plasma.** Collect blood in 2 purple-top (ethylenediaminetetraacetic acid [EDTA]) tubes (4 mL each). After collection, thoroughly mix the tube by gentle inversion 8 times. Label the tube with the Subject's Study ID number. Do not write the subject's name or any other identifying information on the blood tube. Place the tube upright in a rack in the refrigerator (2 to 8°C). Centrifuge for 15 minutes at 4000 x g within 30 minutes of collection. Aliquot plasma into eight 2 mL cryovials and store samples at -80°C.

**Serum.** Collect blood in 2 red-top (serum separator tube [SST]) tubes (5 mL each). After collection, allow blood to clot for 30 minutes. Label the tube with the Subject's Study ID number. Do not write the subject's name or any other identifying information on the blood tube. Place the tube upright in a rack in the refrigerator (2 to 8°C). Centrifuge for 15 minutes at 4000 x g within 30 minutes of collection. Aliquot serum into five 2 mL cryovials and store samples at -80°C.

**Urine.** Aliquot 2 mL into each of 8 different cryovials labeled "Urine".

**Whole Blood.** Collect 1 Cell Preparation Tube (CPT) with Sodium Heparin tube (8 mL). Label the tube with the Subject's Study ID number, study visit, date of visit, and "whole blood". Do not write the subject's name or any other identifying information on the blood tube. Keep at room temperature until pick up by [name] or [name].

**RNA.** Prior to specimen collection: Confirm that informed consent for genetic testing has been obtained prior to the collection of any specimens.

Specimen collection: One 2.5 ml PAXgene tube (RNA extraction)

Invert 8-10 times immediately after drawing

Maintain tubes in upright position at room temperature for a minimum of 2 hours

After 2 hours at room temp, place the PAXgene tube upright in a wire rack to allow for adequate air circulation during freezing in the -20°C freezer for 24 hr.

(NOTE: This must be manual defrost model – not a frost-free model.) Do not use Styrofoam as the tubes tend to stick to the foam and may crack.

Store in -80°C LP#1 freezer for long-term storage.

All specimens must be labeled with a code. Unlabeled specimens will be destroyed.

All specimens must be accompanied by a completed lab sheet.

## 11.0 Data and Specimen Banking

Stored samples will be identified by an indirect identifier (study ID) indefinitely. The study investigators and study coordinators will have access to the link between subject information and study ID. The link between subject information and their study ID will be destroyed 15 years after the study closes.

If stored samples are used in the future to look at new markers the subject and guardian will not be notified nor will they receive the results from the analysis. If the samples are used by other research groups for analysis, the subject and guardian will not be notified. However, any samples that are sent to another researcher will be identified only with a number and will not be able to be traced back to the subject. The subject will not be identified in any publication or report from this study. The subject or guardian can request that blood, urine, and DNA samples be destroyed at any time, prior to 15 years after the study closes, by contacting the study PI.

## 12.0 Data Management and Confidentiality

### 12.1 Subject Population(s) for Analysis

- ☐ Protocol-compliant population (PP): Any subject who received at least 85% of planned doses and attended all scheduled study visits.
- ☐ Safety population (SP): All subjects who receive any amount of treatment.

Safety population (SP) will be used for the primary analyses and the secondary analysis would be based on protocol-compliant population (PP) as part of sensitivity analyses.

## 12.2 Analysis

### **Primary objective**

Outcome variables include AEs/tolerability, 2 most bothersome symptoms, and multi-domain responders index (MDRI) as described in section 9.1. Binary AEs such as hospitalization ( $\geq 1$ ) will be summarized using frequencies/rates by the two period (pre-observation, treatment). The multiple event such as the total number of seizures will be summarized using median with the inter-quartile range (IRQ). For testing changes between the two periods, the McNemar's test (binary event) or Wilcoxon Signed Rank test (multiple events and MDRI) will be used. For continuous outcomes such as laboratory results, a paired t-test and a repeated measures ANOVA will be used. Residual analyses will be conducted to check the model assumption. If it violates assumption, Friedman test (nonparametric) will be used instead.

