### **6.0 Study-Wide Number of Subjects**

Twenty (20) subjects will be enrolled in this pilot study. Individuals who withdraw before Week +8 will be replaced.

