## 9.0 Study Endpoints

### 9.1 Primary and secondary endpoints.

#### Primary endpoints:

Phase 1: Incidence of treatment-emergent adverse events and laboratory values over 8 weeks of treatment to known frequency of anakinra-related AEs in other populations.

Phase 2: Need for dose escalation as determined by within individual change over 8-week treatment period compared to change over 8-week observational period in the 2 most bothersome symptoms for each enrolled patient, selected from measures for the MDRI. Choices are below in bold. These 2 symptoms will be monitored by one or more of the assessments below. If the Minimal Clinically Important Difference (MCID) that is defined below is not achieved after 8 weeks of treatment, or there has been a decrease of more than the MCID between 8 and 16 weeks after an increase greater than MCID at week 8, the dose will be escalated (see Section 27.7). If the MCID is not achieved after 8 weeks on maximum trial dose of 200mg (max dose 8 mg/kg/day), treatment with anakinra may be discontinued (see Section 27.7).

- Sanfilippo **Behavior** Rating Scale (SBRS): MCID = 0.25 SD for each scale
  - Symptoms described in table below:

|                         |                                                                                                                                        |                           |
|-------------------------|----------------------------------------------------------------------------------------------------------------------------------------|---------------------------|
| Body Movements          | Makes large complex movements of their body, such as spinning, twirling or repeatedly bouncing up and down.                            | Movement                  |
| Object Interaction      | Examines or manipulates some novel or unfamiliar objects repeatedly.                                                                   |                           |
| Activity/Routines       | Never plays with one object or engages in one activity for very long.                                                                  |                           |
| Emotional Function      | Expresses emotions inappropriate to the situation.                                                                                     | Social/emotional function |

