### Secondary Endpoints:

Within individual change over 8-week treatment period (on maximum effective and tolerated dose) compared to change over 8-week observational period, and from Day 0 to Week +36 (i.e. treatment phase) in:

1. Incidence of treatment-emergent adverse events and laboratory values over 36-weeks of treatment to known frequency of anakinra-related AEs in other populations.
2. MDRI comprised of:
  - Sanfilippo Behavior Rating Scale (SBRS): Minimal Clinically Important Difference (MCID) = 0.25 SD for each scale
  - Child Sleep Health Questionnaire (CSHQ): MCID = 1-point change 
  - Autism Parenting Stress Index (APSI): MCID = 0.25 SD for Stress Total 
  - PROMIS Fatigue - Parent Proxy Custom Short Form: MCID = 3-point change
  - Movement disorder (e.g. dystonia, chorea, etc.): Parent reported duration and severity. Change in one of two characteristics for +/-1 score, +/-2 score for change in two of the characteristics.
  - Non-communicating Children's Pain Checklist-Revised (NCCPC-R): MCID = 0.25 SD

The MDRI will be calculated as the sum of scores from the components. Subjects will receive a score for each component of the MDRI listed above. A score of 0 will be given for a change in score less than the MCID. A score of +1 (improvement) or -1 (worsening) will be given for a change in score of  $\geq 1$  MCID and  $< 2$  times MCID. A score of +2 (improvement) or -2 (worsening) will be given for a change in score of  $\geq 2$  and  $< 3$  times MCID. A score of +3 (improvement) or -3 (worsening) will be given for a change in score of  $\geq 3$  times MCID. Seizures and movement disorder outcomes will be scored as described above.

3. Individual Clinical Response (ICR) – 5 most impactful clinical problems reported by the caregiver. Sum using 5-point Likert scale for each ICR element.

4. Gait: Qualitative assessment by physical therapist (i.e. improved, no change, worsened).
5. Stair climb/descent: Time and quality of movement.
6. Sleep Diary (1-week recall): Sum of the number of overnight awakenings, average duration of overnight awakenings, and duration of time for initial sleep onset at bedtime.
7. Stooling Survey.

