### **Exploratory objective**

Explanatory outcomes include stool microbiome and Vineland 3. The similar analyses as ones for primary and secondary objectives will be carried out based on data types.

Analyses will be conducted using the programs of SAS v9.4 (SAS Institute, Cary, NC). All tests will be two-tailed and a P value less than 0.05 will be considered statistically significant. The primary outcome will be tested at the 5% significance level. Secondary, exploratory and sensitivity analyses will not be adjusted for multiplicity. Therefore, the results will be interpreted with caution and discussed with recognition of inflated family-wise type I error rate.

Descriptive statistics will be provided on all study data collected from the total cohort (N=20) from the entry to the trial to the completion of 44 weeks follow-up continuous variables will be summarized as numbers of observed and missing values, mean, standard deviation, median, minimum and maximum. Categorical variables will be described as frequencies and percentages.

Any post-hoc, exploratory analyses or deviations which were not identified in this data analysis plan but are completed to support the planned analyses will be clearly identified and the reasons documented.

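### No planned analysis makes the Phase 1 primary comparison with known anakinra adverse-event frequencies; every test in Protocol 12.2 compares the child's own pre-treatment period with treatment

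*Protocol*

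**What the plan says.** Section 9.1 of the Protocol sets the first primary endpoint as follows: "Phase 1: Incidence of treatment-emergent adverse events and laboratory values over 8 weeks of treatment to known frequency of anakinra-related AEs in other populations". Item 1 of the secondary endpoints repeats the external comparator "over 36-weeks of treatment to known frequency of anakinra-related AEs in other populations". That item sits under a stem that announces within-individual change against the observational period.

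Section 12.2, Primary objective, says binary AEs "will be summarized using frequencies/rates by the two period (pre-observation, treatment"), and continues: "For testing changes between the two periods, the McNemar's test (binary event"), or Wilcoxon signed rank for event counts and the MDRI. Laboratory results get a paired t-test and repeated measures ANOVA, with Friedman's test as fallback. The general rule is "All tests will be two-tailed and a P value less than 0.05 will be considered statistically significant", and the closing part of 12.2 says the primary outcome is tested at the 5% level.

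Three other places bear on this:

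- Section 12.3 gives 95% confidence-interval precision for AE proportions during treatment, but names no reference rate.
- Section 15.2 lists reactions reported with anakinra, without frequencies.
- Footnote f of the Schedule of Events restricts recording before the first dose to serious events tied to protocol procedures. Section 13.3 requires all AEs in the study period to be recorded.

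**The concern.** The endpoint asks whether children with MPS III have more AEs on anakinra than other populations do. McNemar's null is that a child's risk on treatment equals the same child's risk before treatment. That is a different hypothesis, and no external frequency enters it. The Wilcoxon, paired t and ANOVA analyses share this comparator.

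This is not a detail left to a later analysis plan. Section 12.2 names the tests for the primary objective, and they answer another question.

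The chosen comparator has problems of its own. An injection-site reaction cannot happen before the first injection. Under footnote f, most other AEs before dosing would not be recorded either. For such events the test mainly asks whether anakinra has side effects at all. A significant result could be read as a safety signal when incidence is no higher than already known, and a non-significant one as reassurance when it is higher.

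**Working it through.** **Inputs.** n = 20 (Protocol 6.0: "Twenty (20) subjects will be enrolled in this pilot study"); two-sided alpha 0.05 (12.2). Known frequencies are not given, so I use 5% to 50% as an assumed range. It includes the 5% to 15% that 12.3 uses for AE proportions.

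**Step 1: the plan's own figure.** Section 12.3 states a margin of error of 13% to 18% for proportions of 5% to 15%. Clopper-Pearson half-widths at n = 20 are:

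- 1/20: (24.9% − 0.1%)/2 = 12.4%
- 3/20: (37.9% − 3.2%)/2 = 17.3%

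Both lie within one percentage point of the stated values; the plain Wald formula gives 9.6% and 15.7%. So 12.3 is consistent with an exact or corrected interval on the on-treatment proportion.

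**Step 2: when exact McNemar rejects with an empty pre-treatment period.** All discordant pairs then point one way, and with k affected children the two-sided p-value is 2 × 0.5^k. For k = 5 this is 0.0625; for k = 6 it is 0.031. The test rejects at 6 or more of 20, so the rejection probability is P(X ≥ 6) with X ~ Bin(20, p).

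**Step 3: true incidence equal to the known frequency.** There is no excess to find:

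| True = known | Exact McNemar rejects |
|---|---|
| 5% | 0.03% |
| 10% | 1.1% |
| 15% | 6.7% |
| 20% | 19.6% |
| 30% | 58.4% |
| 50% | 97.9% |

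The uncorrected large-sample version rejects at 4 or more events, which gives 35.2% at 15% and 89.3% at 30%. If 10% of children have the event before treatment (periods independent), exact McNemar rejects 18.8% at 30% and 69.4% at 50%.

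**Step 4: a true excess of a rarer AE, empty pre-treatment period.** The comparison is a two-sided exact binomial test against the known frequency:

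- Known 5% (binomial rejects at 4 or more), true 20%: McNemar P(X ≥ 6) = 19.6%; binomial P(X ≥ 4) = 58.9%.
- Known 10% (rejects at 5 or more), true 30%: McNemar 58.4%; binomial P(X ≥ 5) = 76.2%.

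**Step 5: an AE with disease background.** Take known 15%, background 30% and true on-treatment rate 40%, with periods independent and pre-treatment events recorded. Exact McNemar rejects 5.0%; the binomial test against 15% rejects at 7 or more, giving P(X ≥ 7) = 75.0%. If anakinra changes nothing (30% before and on treatment), the same binomial test still rejects P(X ≥ 7 | 0.30) = 39.2%. Much of the apparent advantage here is therefore sensitivity to MPS III itself.

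**The case against.** Several points on the other side have weight.

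- Section 9.1 does not ask for a hypothesis test, and 12.3 already foresees estimating on-treatment AE proportions with 95% intervals. That is half of what an external comparison needs. This stands, and it limits the defect to the missing link to reference frequencies and the mismatched tests.
- Section 12.2 illustrates its AE tests with hospitalization and seizures. MPS III produces these without the drug, and 13.2 lists many expected disease events. For them the within-child comparison helps separate drug from disease, as Step 5 shows. This stands, and is why that comparison should be kept as context. Seizures also have their own real-time record (10.12), so footnote f does not empty their pre-treatment period.
- In the 5% to 15% range of 12.3, exact McNemar seldom rejects when incidence equals the known rate. This stands; the false alarm belongs to common AEs.
- This is a feasibility-sized open-label pilot, and the stopping rules in 13.4 are event-based. No stated decision turns on a McNemar p-value. This lowers the stakes but does not align the analysis with the primary endpoint.

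A reader might infer that McNemar is the only AE test, or that the safety question goes unanswered in both directions. The documents support neither: Wilcoxon covers event counts, although with the same comparator, and 12.3 supplies the on-treatment estimate. Nor do false alarm and missed excess bear strongly on the same AE. The first needs a common event with a near-empty pre-treatment period, the second a rarer event or a high recorded background.

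**Conclusion.** The point holds. The Phase 1 primary endpoint is defined against an external frequency, and no planned analysis makes that comparison. This follows from the text alone, whether footnote f or 13.3 governs recording before treatment.

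The numerical consequences are conditional. With n = 20, exact McNemar and an empty pre-treatment period, the test can reject without any excess for common AEs (58% at 30%, 98% at 50%). It can miss an excess of rarer ones (20% against 59% for known 5%, true 20%). Between 5% and 15% the false-alarm problem is small with the exact test. All rates are assumed, and the protocol does not say which McNemar version applies.

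**What to change.** In 12.2, make the primary Phase 1 analysis of AEs the proportion of children with each measured AE class over 8 weeks of treatment, with exact 95% confidence intervals. Set these beside a table of reference frequencies fixed before analysis. Do the same over 36 weeks for secondary item 1. Leave out classes that are not measured: 15.2 lists anti-anakinra antibodies, which 10.4 says will not be assayed in this pilot. Treat any binomial p-values as unadjusted and supportive.

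Keep the pre-treatment versus treatment comparison as descriptive context for disease-background events such as seizures and hospitalization, and say that an excess over the external rate may reflect MPS III and not the drug.

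Reconcile footnote f with 13.3 on AE recording before treatment, and the within-individual stem of the secondary endpoints in 9.1 with its item 1.

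The cost is revised wording and one reference table; sample size, visits and dosing are unaffected. The drawback is that reference rates come from other populations and ages, a limit 9.1 already accepts.

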f After written informed consent but before study treatment initiation, only SAEs associated with protocol-imposed interventions will be recorded. After study drug initiation, all AEs, SAEs, and pregnancy will be recorded until week 44 or the Early Termination visit. If a subject is discontinued from the study prematurely, AEs and SAEs will be recorded at the Early Termination visit.

g During these contacts, study staff will ask about dose administration and seek information on AEs and SAEs by specific questioning. Information on all AEs and SAEs should be recorded in the subject's medical record and on the AE eCRF.

h Diaries will be completed at week -6 to avoid the potential impact of travel on these outcomes.

i Plasma and serum samples collected and stored for PK and anti-drug antibody studies.

j Buffy coat will only be collected on Week -8, Day 1, and Week +36.

k Week +24 safety labs only if dose was increased at week +16.

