**13.3 Recording of Adverse Events**

At each contact with the subject, the Investigator must seek information on AEs by specific questioning and, as appropriate, by examination. Information on all AEs should be recorded immediately in the source document, and also in the appropriate AE module of the case report form (CRF). All clearly related signs, symptoms, and abnormal diagnostic procedures results should be recorded in the source document, though should be grouped under 1 diagnosis.

All AEs occurring during the study period must be recorded. The clinical course of each event should be followed until resolution, stabilization, or until it has been determined that the study treatment or participation is not the cause. Serious adverse events that are still

ongoing at the end of the study period must be followed up to determine the final outcome. Any SAE that occurs after the study period and is considered to be possibly related to the study treatment or study participation should be recorded and reported immediately.

Toxicity and AEs will be classified according to the National Cancer Institute (NCI) Common Toxicity Criteria (CTC) V 4.1 and causality will be classified as:

Unrelated - The AE is likely NOT related to study treatment or procedures

Related - The AE is likely related to study treatment or procedures

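### Under the Schedule of Events footnote, AEs before and after the first dose are recorded by different rules, which biases the paired AE test in Section 12.2 toward harm; Section 13.3 conflicts with that footnote

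*Protocol*

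**What the plan says.** Section 12.2 (Primary objective) takes AEs and tolerability as one of its outcomes. Binary AEs, of which hospitalization is the only example given, "will be summarized using frequencies/rates by the two period (pre-observation, treatment"). The next step is a within-subject test: "For testing changes between the two periods, the McNemar's test (binary event) or Wilcoxon Signed Rank test (multiple events and MDRI) will be used".

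What counts as a recorded AE is fixed in two places that do not agree:

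- Section 10.2, Schedule of Events, footnote f: "After written informed consent but before study treatment initiation, only SAEs associated with protocol-imposed interventions will be recorded". From the first dose until Week 44 or early termination, the same footnote records all AEs and SAEs.
- Section 13.3: "All AEs occurring during the study period must be recorded".

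The AE row of the Schedule of Events is marked at Week -8 and Day +1, but the row carries footnote f, so the marks do not settle which rule applies before dosing.

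On timing, Section 10.1 gives an 8-week observation period followed by 36 weeks of treatment. Section 9.1 sets the Phase 1 primary endpoint over the first 8 weeks of treatment and lists as a secondary endpoint "Incidence of treatment-emergent adverse events and laboratory values over 36-weeks of treatment". The test paragraph in Section 12.2 says only treatment, without a length.

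**The concern.** A paired test of a change between two periods assumes that an event has the same chance of being counted in each. Under footnote f it does not. An admission for pneumonia four weeks before the first dose would not go on the AE form, because it has nothing to do with a protocol procedure. The same admission four weeks after the first dose would. Subjects with an AE-form event on treatment only then come partly from the recording rule, and subjects with one before treatment only almost disappear.

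The study has one arm, so the observation period is its only internal comparator for AEs. Background illness is expected here: Section 13.2 lists upper respiratory infection, fever, vomiting and diarrhea among expected events, and Appendix A refers to a large number of disease-related SAEs, including hospitalization. A paired result that counts this background on one side only would be read as a drug effect. AEs that were never collected before dosing cannot be restored at analysis.

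**Working it through.** **Inputs.** Sample size: "Twenty (20) subjects will be enrolled in this pilot study" (Section 6.0). Test level: "All tests will be two-tailed and a P value less than 0.05 will be considered statistically significant" (Section 12.2). Recording rule: footnote f as written, with the pre-dose count taken as zero. That is a simplification, since SAEs tied to protocol procedures would still be counted. The background 8-week risk *q* of at least one AE-form event is not given in the protocol as a background rate. It is an assumption and is shown as a range.

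**The plan's own figure.** Section 12.3 gives no error rate for the paired test. It gives a margin of error of 13% to 18% for AE proportions of 5% to 15% at n = 20. A Wilson interval with continuity correction gives half-widths of 13.3% (1/20) and 17.5% (3/20), so the figure is reproduced to within a point; a plain Wald interval gives 9.6% and 15.6%. Nothing below depends on it, except that 5% to 15% is the only AE range the protocol offers.

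**Step 1: rejection threshold.** Let *b* be the number of subjects with an event on treatment only and *c* the number with one before treatment only. With *c* = 0 by rule:

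- Exact two-sided McNemar: p = 2 × 0.5^b. At b = 5, p = 0.0625; at b = 6, p = 0.031. Six subjects suffice.
- Uncorrected chi-square: (b − c)²/(b + c) = b. At b = 3, p = 0.083; at b = 4, p = 0.046. Four subjects suffice.
- Exact Wilcoxon signed rank on AE-form counts, with every non-zero difference positive: p = 2 × 0.5^k for k subjects with any event, so again six.

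Section 12.2 does not say which version of McNemar's test is meant, so both are shown.

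**Step 2: chance of false harm with no drug effect.** On treatment, b follows Binomial(20, q). The chance is P(b ≥ 6) for the exact test and P(b ≥ 4) for the chi-square test.

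| Assumed 8-week risk q | Exact McNemar | Uncorrected chi-square |
|---|---|---|
| 5% | 0.03% | 1.6% |
| 10% | 1.1% | 13% |
| 15% | 6.7% | 35% |
| 20% | 20% | 59% |
| 30% | 58% | 89% |
| 40% | 87% | 98% |
| 50% | 98% | 99.9% |

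**Step 3: the same test with like-for-like recording.** Give both periods the same q and the same 8 weeks, and treat them as independent (an assumption). Over background risks from 5% to 90%, the total false-positive rate is at most about 2.3% (exact) or 4.9% (chi-square), and half of that points to harm. The excess in the table therefore comes from the recording rule.

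**The case against.** Several points stand against a stronger statement.

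- **An empty pre-dose cell is not established.** Section 13.3 asks for all AEs, Section 13.2 defines an AE as arising during the course of the study, history is updated at each visit (Section 10.3), and MPS III-related procedures are recorded from consent (footnote b). Staff who follow Section 13.3 would collect pre-dose AEs. This stands: what the text proves is a conflict. It does not remove the problem, because footnote f is the specific rule for the pre-dose period, and visit history is not the same as AE-form entry under the same questions.
- **A false harm signal is not certain.** A reader might infer that the test will show harm. If the 5% to 15% of Section 12.3 is taken as an 8-week risk, the exact test misleads in only 0.03% to 6.7% of trials. The high figures need risks of 30% or more, which the protocol does not state. This stands; only the direction of the bias is fixed by the rule.
- **Most outcomes under the quoted test are untouched.** The example of a multiple event is seizures, which caregivers log in real time (Section 10.12). MDRI components and laboratory values are measured in both periods. This stands; the defect reaches AE-form events only.
- **The Phase 1 endpoint does not use the pre-dose count.** Section 9.1 compares treatment-emergent AEs with known frequencies in other populations, and Section 12.3 bases precision on the treatment period. A reader might infer that the primary safety result cannot be interpreted. The protocol does not support that.
- **The 8-against-36-week comparison is only a possible reading.** Section 12.2 refers to Section 9.1, which ties the primary safety endpoint to 8 weeks. If all 36 weeks were used, a constant 8-week risk of 15% would become 1 − 0.85^(36/8) = 52%, and even with equal recording the exact test would signal false harm in about 57% of trials. The protocol does not say that this test is intended, so the figure is only a reason to state the window.

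**Conclusion.** The concern holds in a limited form. Section 12.2 plans a paired pre/post test of AEs, and footnote f, if followed, counts the two periods by different rules, so the comparison is biased toward harm. Section 13.3 contradicts the footnote, and the protocol does not say which prevails.

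The size depends on the background risk. With no drug effect and 20 subjects, false harm from the exact test runs from 0.03% of trials at an assumed 8-week risk of 5% to 98% at 50%; the uncorrected chi-square runs from 1.6% to 99.9%. These figures assume a pre-dose count of zero and an 8-week treatment window.

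The damage is confined to the paired test of AE-form events. The external Phase 1 comparison, seizure-diary counts, MDRI and laboratory values stand. This should be fixed, but it does not undermine the safety evaluation as a whole.

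**What to change.** 1. Reconcile footnote f and Section 13.3 into one rule: all AEs and SAEs are recorded from the Week -8 visit, with the same questions before and after the first dose.
2. State in Section 12.2 that the paired AE test uses equal windows, Week -8 to Day 1 against Day 1 to Week +8, and that 36-week AEs are reported as exposure-adjusted rates.
3. If pre-dose AEs were not collected under the same rule, drop the paired AE test and report on-treatment incidence with exact confidence intervals. The current version is dated November 2023 against an original of October 2019, so collection may be well advanced, although the protocol does not say so. This fallback works either way.

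The cost is one footnote, a matching line in Section 13.3 and two or three sentences in Section 12.2, plus a few more AE entries per subject. The AE form and the four-weekly contacts with AE questions (footnote g) already exist.
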